### Sub group analysis

• Patient participant age (years):- < 45, 45 to 64, ≥ 65;

• Smoking:- non-smoker or smoker;

• Periodontal disease severity:- no clinical signs, presence of gingival bleeding on probing, pocket depth ≤ 4 mm or > 4 mm;

• Intervention provider:- dentist or practice hygienist.

### Economic analyses

#### **
*Estimation of costs*
**

Health care resource utilisation data will be combined with unit cost information for the use of specific resources provided by the participating practices; use of routine data sources and patient participants’ time, travel and out-of- pocket costs (for the latter this will only include costs not otherwise collected from participating practices). Data on costs for each area of service use will summed to provide an average cost per patient participant. Sensitivity analysis will be used to explore the impact of price paid by patient participants on the uptake of dental services. These data will be used to consider whether use of services systematically varies by the extent of NHS coverage.

#### **
*Estimation of benefits*
**

The benefit side of the economic evaluations will firstly be based upon the effectiveness data detailed in *outcome measures*. Patient’s may place different weight on these different outcomes and also have preferences for the way in which services are organised. A DCE will be used to provide a framework to weight different process and outcomes measures. DCEs are increasingly used in the evaluation of health care interventions to produce overall benefit scores for treatments as well as examine the absolute and relative importance of different outcomes considered as important. This approach has been adopted as measures such as quality adjusted life years typically used in economic evaluations may not be sufficient to capture the strength of preferences for differences in the process and outcomes of care associated with each intervention. Briefly, DCEs describe an intervention in terms of a number of characteristics or outcomes (attributes). The extent to which an individual values an intervention depends upon the levels of these characteristics [22,23]. The technique involves presenting choices to individuals that imply a trade-off in terms of the levels of the attributes. Experimental design techniques are used to define the set of choices presented to respondents and logit regression techniques are used to analyse the response data.

The DCE will be administered to a separate sample of the public obtained from an online marketing company. Respondents will be part of a large online panel who will be invited to complete on online survey via email. Panellists are rewarded for the time they take to complete the survey through a structured incentive scheme. They receive a cash reward for participating in individual surveys – the amount is clearly stated in the invitation email and related to the survey length, interest and complexity (range between 50p-£5). Each panellist will be assigned an individual ID, allowing the company to monitor panellist activity and distinguish between contact rate (e.g. those who were initially contacted and did/did not complete the survey) and completion rate (e.g. those who completed the survey and did not drop out). This is an approach that we have successfully used in previous studies and overcomes the problems caused by very poor response rates from samples drawn from the general population.

The sample size required reflects the need for the sample to be larger than the number of independent variables [24]; provide an adequate sample for each predetermined subgroup e.g. dental attendance (regular, non-regular), non-smoker or current smoker, social economic group (high, medium and low), country (England, Scotland) (19 subgroups in total and 30–100 per subgroup [25]. Allowing for individuals to be present in a number of groups, the questionnaire will be administered online and a maximum of 950 individuals (19 × 50) completed questionnaires will be sought.

In addition to the outcomes included in the DCE one further attribute included will be patient cost. By including this attribute, the willingness to pay (WTP) for a change in the level of any other attribute will be estimated. This information will be combined with the clinical outcomes provided obtained from the trial for each participant and about type of care provided to provide an estimate of the mean WTP for each intervention considered.

#### **
*Costs and benefits to the practitioner participant*
**

Different frequencies of PI visits will impact upon clinicians’ costs and benefits. The effect on incomes, job satisfaction and changes to the level of fees on the provision of PI will be assessed using self-reported questionnaires administered to clinicians over the duration of the trial.

#### **
*Presentation of results*
**

Results will be presented both as a cost-consequence analysis (presentation of costs and outcomes, including those to practitioners) and as incremental net benefits. Net benefits will be calculated by combining estimates of mean WTP with estimates of mean cost for each intervention. The intervention with the greatest net benefit would be considered the most efficient. The evaluation will include both deterministic and probabilistic sensitivity analysis, using methods developed for previous analyses [26].

### Sample size

An OHA exploratory trial in the same population as the proposed trial demonstrated that at baseline 35% of gingival sites were bleeding on probing with sd = 25% [27]. The PI Cochrane review suggested that a reduction of 15% of sites with bleeding was a plausible reduction for 6 monthly PI [12]. If the effect is assumed linear, halving the number of PIs should half the expected difference of 15% of sites. If the effect is non linear and larger than 7.5%, the trial will be adequately powered. If the effect is smaller it would be of questionable clinical significance. There is some evidence that personalised OHA can reduce the number of gingival sites bleeding on probing by approximately 7.5% [27]. The following calculations are based on estimating main effects from the trial. All calculations assume a significance level of 2.5% to give some protection against multiple testing.

#### **
*OHA*
**

To calculate the sample size required to estimate the main effect of OHA, it is recognised that the data are contained within a cluster RCT. Assuming a conservative estimate of the intracluster correlation (ICC) of 0.0531, a cluster RCT of 50 dentists collecting information from 25 patient participants each (25*25 = 625 patients per arm) will have 90% power to detect a difference of 7.5%. Should the correlation be 0.1, the trial will still have approximately 80% power to detect a difference of 7.5%.

#### **
*PI*
**

Given that the comparison of routine versus personalised OHA requires 625 patient participants in each arm, equal randomisation 1:1:1 (no PI; 6 monthly; 12 monthly) of patient participants implies 208 in each of the six groups. Assuming no interaction effect, the corresponding PI groups can be combined across both routine and personalised advice groups giving 416 patients allocated to each PI group. Assuming a sample size of 416 in each group, the trial will have in excess of 95% power for each pairwise comparison to detect a difference of 7.5% in the percentage of gingival sites that bleed on probing.

#### **
*Interaction*
**

We do not anticipate a substantive interaction effect between the PI interventions and the personalised OHA. Assuming an ICC of 0.05, the trial has 80% power to detect an interaction effect of 7.5%. Should the ICC be 0.1, the trial has approximately 80% power to detect an interaction of 10%.

At trial endpoint the total number of dentists required is 50 and the total number of participants is 1248 (6*208). Our previous trials in general dental practice suggests that we may lose a small number of dental practices in the trial for reasons such as practices amalgamating with other practices or restricting NHS patients. We have therefore very conservatively assumed 17% attrition for dentists and 20% for participants. These assumptions imply that 60 dentists and 1860 participants will be required. Each dentist will be required to recruit on average 31 participants to ensure 25 at follow-up.

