## Analysis plan

### Statistical analyses

The factorial design of the trial allows for the main effects and interactions between interventions to be examined. Reflecting the clustering in the data, the outcomes will be compared using multilevel models, with adjustment for minimisation variables [19]. Statistical significance will be at the 2.5% level and corresponding confidence intervals will be derived. All participants will remain in their allocated group for analysis (intention to treat). Subgroup analyses using interaction terms will explore the possible effect modification of a number of factors (See Sub group analysis), all using stricter levels of statistical significance (p < 0.01). Missing patient reported outcomes will not be imputed at the follow-up time points for the primary analyses. However, we will investigate the mechanism of missingness using regression models [20] and apply an appropriate missing data model as a sensitivity analysis [21]. All trial analyses will be according to a statistical analysis plan that will be agreed in advance by the Trial Steering Committee (TSC). The Data Monitoring and Ethics Committee (DMEC) will meet at 9, 24 and 36 months to review progress and recommend any divergences from planned trial design.

A single main analysis will be performed at the end of the trial when all follow-up has been completed. Unblinded interim analyses will be conducted for the DMEC meetings as required.

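### Power for the OHA comparison at an ICC of 0.1 is about 74% at the protocol's own 2.5% level, not approximately 80%

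*Protocol article*

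**What the plan says.** The Sample size section of the protocol article fixes the level for everything in it: "All calculations assume a significance level of 2.5% to give some protection against multiple testing". The Statistical analyses section carries the same level into the analysis: "Statistical significance will be at the 2.5% level and corresponding confidence intervals will be derived".

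The inputs for the OHA comparison are also in the Sample size section:

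- Variability: "at baseline 35% of gingival sites were bleeding on probing with sd = 25" (per cent).
- Effect: "personalised OHA can reduce the number of gingival sites bleeding on probing by approximately 7.5" (per cent of sites).
- Design: "a cluster RCT of 50 dentists collecting information from 25 patient participants each (25*25 = 625 patients per arm").
- Base-case ICC: "Assuming a conservative estimate of the intracluster correlation (ICC) of 0.0531", for which 90% power is claimed. The Interaction paragraph uses 0.05.

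The fallback claim follows: "Should the correlation be 0.1, the trial will still have approximately 80% power to detect a difference of 7.5" (per cent).

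The 50 dentists and 25 patients each are numbers at trial endpoint. The section inflates them afterwards to 60 dentists and 1860 participants for attrition, so no further loss has to be deducted.

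**The concern.** Moving the ICC from about 0.05 to 0.1 raises the design effect for clusters of 25 from 2.2 to 3.4, so the effective sample size falls by about a third (1 − 2.2/3.4 = 35%). A fall in power from 90% to only 80% looks too small for that loss.

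Personalised versus routine OHA is primary objective (a). It is the only primary comparison randomised by dentist, so it is the one most exposed to the ICC. This sentence is the protocol's reassurance that the comparison tolerates a higher ICC. If the figure is too high, the steering and data monitoring committees would see a margin that is not there. A null OHA result at an ICC near 0.1 would also be read with more confidence than the design supports.

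**Working it through.** **Inputs** (Sample size section): k = 25 dentists per arm, m = 25 patients per dentist, n = 625 per arm, SD = 25 points, difference = 7.5 points, significance level 2.5%. Sidedness is not stated and is settled by step 1.

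**Formulas**

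- Design effect: DE = 1 + (m − 1) × ICC
- Standard error of the difference: SE = 25 × √(2 × DE / 625)
- Power, normal approximation: Φ(7.5/SE − z), with z = 2.241 for two-sided 2.5% and z = 1.960 for two-sided 5%
- As a check: noncentral t with 2 × 25 − 2 = 48 degrees of freedom and noncentrality 7.5/SE

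**Step 1: reproduce the 90%**

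| ICC | DE | SE | Power, two-sided 2.5% | Power, two-sided 5% |
|---|---|---|---|---|
| 0.05 | 2.200 | 2.098 | 90.9% (t: 89.2%) | 94.7% (t: 93.9%) |
| 0.0531 | 2.274 | 2.133 | 89.9% (t: 88.1%) | 94.0% (t: 93.1%) |

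The stated 90% matches two-sided 2.5% and does not match 5%. One-sided 2.5% is numerically the same as two-sided 5%, so it does not match either. Two-sided 2.5% is therefore the working reading. Which of the two ICC values was meant makes no difference to step 2.

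**Step 2: same method and level at ICC 0.1**

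- DE = 1 + 24 × 0.1 = 3.4
- Effective n = 625/3.4 = 183.8 per arm
- SE = 25 × √(2 × 3.4/625) = 2.608
- 7.5/2.608 = 2.876
- Two-sided 2.5%: Φ(2.876 − 2.241) = Φ(0.635) = **73.7%** (t: 71.2%)
- Two-sided 5%: Φ(2.876 − 1.960) = Φ(0.916) = **82.0%** (t: 80.5%)

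**Step 3: what the design does support at two-sided 2.5%**

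- Largest ICC that keeps 80% power for 7.5 points: about 0.08. At ICC 0.08, DE = 2.92, SE = 2.417 and power is 80.6%. With the t reference that ICC gives 78.2%, and the limit is about 0.075.
- Difference detectable with 80% power at ICC 0.1: (2.241 + 0.842) × 2.608 = 8.04 points (about 8.3 with t).
- Size needed for 80% power for 7.5 points at ICC 0.1: 212 per arm without clustering, × 3.4 = 721 patients, and 721/25 ≈ 29 dentists per arm, against the planned 625 and 25.

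**The case against.** The strongest reply is about weight. The sentence is a hedged sensitivity statement about a pessimistic ICC. The sample size rests on the base case, which reproduces, and the error alters no recruitment target and no analysis. That stands: the damage is confined to one fallback figure.

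The second reply is that power near 80% at ICC 0.1 and two-sided 2.5% is within reach under modest departures from the stated inputs (normal approximation):

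- 29 retained dentists per arm instead of 25 give 80.4%. The protocol recruits 60 and regards its 17% dentist attrition as very conservative.
- A correlation of about 0.36 between baseline covariates and outcome gives 80.0%. The model adjusts for the minimisation variables, two of which describe baseline periodontal status.
- An SD of about 23.3 gives 80.1%.

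These show that the practical risk may be smaller than the bare figure suggests. They do not rescue the sentence. The Sample size section invokes none of them, and each would raise the base case to about 94% to 95%, above its stated 90%.

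Third, sidedness is not stated. One-sided 2.5% would give 82.0% at ICC 0.1, but it would put the base case at 94% to 95%. Both printed figures could then be read only as minimums, although the section words neither that way. Why the figure is wrong cannot be known. A 5% level fits the number, but loose rounding is also possible.

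**Conclusion.** The figure is wrong as written. With the protocol's own inputs and level, power for the OHA main effect at ICC 0.1 is 73.7% (71.2% with t on 48 degrees of freedom), against approximately 80% stated. The shortfall is 6 to 9 percentage points.

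The result assumes a two-sided test, which is inferred from the 90% figure, together with equal clusters of 25, an SD of 25 and no variance reduction from covariates. Equal cluster sizes favour the protocol. If the coefficient of variation of cluster size were 0.3 to 0.5 (an assumption; the document gives none), DE = 1 + ((1 + CV²) × 25 − 1) × 0.1 would be 3.63 to 4.03, and power 71% to 66%.

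**What to change.** Replace the fallback sentence with wording such as: *Should the ICC be 0.1, power at the two-sided 2.5% level is about 74% for a difference of 7.5 percentage points and 80% for about 8.0 points; 80% power for 7.5 points is kept up to an ICC of about 0.08 (normal approximation).* If t-based figures are preferred, use about 71%, 8.3 points and 0.075 throughout, so that the two methods are not mixed.

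Alternatively, keep 80% and state the significance level or variance assumption that produces it, and apply the same assumption to the base case. A remark that baseline adjustment may recover some power is reasonable if the assumed correlation is given. State in the same place that tests are two-sided.

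The cost is one sentence and a less favourable fallback figure. No extra dentists or patients and no change to the analysis are needed.

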### Objectives

The primary objectives are to test the effectiveness and cost effectiveness of the following dental management strategies:

a) Personalised OHA versus routine OHA;

b) 12 monthly PI versus 6 monthly PI;

c) No PI versus 6 monthly PI.

The secondary objectives include:

d) To test the effectiveness and cost-effectiveness of a combination of personalised OHA with different time intervals for PI;

e) To measure dentist/hygienist beliefs relating to giving OHA, PI and maintenance of periodontal health.

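### The stated 80% power for a 7.5-point OHA-by-PI interaction is about 49% on the protocol's own inputs

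*Protocol article*

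**What the plan says.** The Interaction paragraph of the Sample size section makes two claims: "Assuming an ICC of 0.05, the trial has 80% power to detect an interaction effect of 7.5" (percentage points), and "Should the ICC be 0.1, the trial has approximately 80% power to detect an interaction of 10" (percentage points). It adds that no substantive interaction is expected.

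The inputs are in the same section:
- **Significance level:** "All calculations assume a significance level of 2.5% to give some protection against multiple testing".
- **Spread of the outcome:** "at baseline 35% of gingival sites were bleeding on probing with sd = 25" (per cent).
- **Cluster structure:** "a cluster RCT of 50 dentists collecting information from 25 patient participants each (25*25 = 625 patients per arm").
- **Cell size:** equal PI allocation "implies 208 in each of the six groups".

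The Methods/Design section randomises OHA by dentist and PI by individual patient, so each dentist has patients in all three PI groups. For the PI main effects the plan pools: "Assuming no interaction effect, the corresponding PI groups can be combined across both routine and personalised advice groups". Secondary objective (d) is "To test the effectiveness and cost-effectiveness of a combination of personalised OHA with different time intervals for PI".

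**The concern.** An interaction is a difference between two differences, so it involves four cells of 208. Its variance is four times that of one cell mean, whereas a simple comparison of two cells has only twice that variance. Yet 80% at 7.5 points is close to what a two-cell comparison would give.

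The two interaction sentences also fit together badly. Moving the detectable effect from 7.5 to 10 points at the same power implies a variance ratio of (10/7.5)² = 1.78 between ICC 0.1 and ICC 0.05.

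The figure matters because it tells the steering committee and later readers how informative a null interaction result would be. At 80% power, an interaction of 7.5 points would be missed one time in five. At 49% it would be missed about half the time. The size is not arbitrary: 7.5 points is the target difference for OHA and for halving PI frequency.

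**Working it through.** **Inputs.** SD 25 points, 208 per cell, 25 patients per dentist, 625 per OHA arm, 416 per pooled PI group. The 2.5% level is taken as two-sided, with critical value 2.2414. Power = Φ(δ/SE − 2.2414).

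**Step 1. Do these inputs reproduce the plan's main-effect figures?**
- OHA, 625 per arm, SE = 25 × √(2 × [1 + 24 × ICC]/625). At ICC 0.05 the SE is 2.098 and power 90.9%. At the printed 0.0531 it is 2.133 and 89.9%. Stated: 90%.
- PI, 416 per group, SE = 25 × √(2/416) = 1.733, power 98.1%. Stated: over 95%.

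Both agree, so SD 25 and a two-sided 2.5% level are a sound reading of the plan.

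**Step 2. The 7.5-point interaction at ICC 0.05.** PI varies within dentist. Under a random dentist intercept the dentist effect therefore cancels, leaving residual variance SD² × (1 − ICC):
- SE = √(4 × 625 × 0.95/208) = 3.379
- Power = Φ(7.5/3.379 − 2.2414) = 49.1%

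The SE needed for 80% power is 7.5/(2.2414 + 0.8416) = 2.433.

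**Step 3. Other readings of the same claim** (7.5 points, ICC 0.05).

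| Reading | Power |
|---|---|
| Clustering ignored (SE 3.467) | 46.9% |
| Design effect 1 + (25/3 − 1) × 0.05 = 1.37 | 34.8% |
| Design effect 1 + 24 × 0.05 = 2.2 | 21.7% |
| Two-sided 5% (same as one-sided 2.5%), within-dentist | 60.2% |
| One-sided 5%, within-dentist | 71.7% |
| All 1860 recruited, 310 per cell, within-dentist | 68.0% |
| Any PI versus none, within-dentist | 62.6% |
| 2-df test, one PI group differing by 7.5, within-dentist | 51.6% |
| Two single cells, 208 v 208, clustering ignored (SE 2.451) | 79.3% |

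Only the last row comes to about 80%, and it is not an interaction.

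**Step 4. The companion sentence** (10 points, ICC 0.1).
- SE = √(4 × 625 × 0.90/208) = 3.289
- Power = Φ(10/3.289 − 2.2414) = 78.8%, so this sentence reproduces.
- By the same method, 10 points at ICC 0.05 gives Φ(10/3.379 − 2.2414) = 76.4%. A smaller effect of 7.5 points cannot then have 80% at that ICC.

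**Step 5. What the design can detect with 80% power.** 3.083 × 3.379 = 10.4 points at ICC 0.05, and 3.083 × 3.289 = 10.1 points at ICC 0.1. Reaching 80% for 7.5 points at ICC 0.05 would need 4 × 625 × 0.95 × (3.083/7.5)², about 402 evaluable patients per cell, against 208.

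**The case against.** **Covariate adjustment could help.** SD 25 is a baseline figure, and the Statistical analyses section adjusts for the minimisation variables, which include absence of bleeding. Power rises to 61% at residual SD 22 and 70% at SD 20. Reaching 80% needs SD 18, with about 48% of the variance explained. The protocol claims no such gain, and its main-effect figures reproduce without one. This qualifies the 49% but does not rescue the 80%.

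**The interaction might be coded as half the difference of differences.** A true contrast of 15 points then has about 99% power within dentist. Applying the full design effect of 2.2 (SE 5.142) gives Φ(15/5.142 − 2.2414) = 75%. That is nearer, but still not 80%. It needs an unstated coding and also a between-dentist inflation of a within-dentist contrast.

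**Stronger readings that a reader might infer, and that the protocol does not support:**
- *That a non-significant test is meant to license pooling.* The protocol pools by stated assumption and gives no test-based rule.
- *That objective (d) cannot be tested.* The interaction test can be run, with about even odds at 7.5 points. The objective can also be read as comparing combined strategies. PI intervals compared within one OHA arm have about 82% power for 7.5 points (SE = √(2 × 625 × 0.95/208) = 2.39). Single cells compared across OHA arms have about 65% (SE 2.87, design effect 1.37).
- *That the dependence on ICC is stated backwards.* Under a random intercept with total SD fixed, a higher ICC slightly helps this contrast. If the PI effect varies between dentists, that no longer follows and power falls. The protocol says only that multilevel models will be used, and its 10-point sentence is correct on the simpler model.
- *That 7.5 points equals every main effect.* For 6-monthly PI the section cites 15 points as plausible, so against no PI it is half the expected effect.

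**Conclusion.** The statement of 80% power for a 7.5-point interaction at ICC 0.05 is wrong as written; the figure is about 49%. This rests on SD 25, 208 evaluable patients per cell, a two-sided 2.5% level, a random dentist intercept with PI balanced within dentist, and no gain from covariates. PI allocation is not minimised on dentist, so the cancellation in Step 2 is approximate; ignoring clustering altogether moves the figure only to 47%.

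A two-cell calculation used in place of the interaction would explain the 80%, but the protocol does not show its method, so that remains a conjecture.

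The reach is limited. The section bases its calculations on main effects, so the interaction figure does not drive the 50 dentists or the 1248 and 1860 participants. The PI main-effect power and the OHA power at ICC about 0.05 are unaffected.

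**What to change.** Replace the two interaction sentences with one statement on a single method:

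> With 208 per cell the trial has about 49% power to detect an interaction of 7.5 points and about 80% power to detect about 10.4 points at ICC 0.05 (about 10.1 points at ICC 0.1), assuming a random dentist intercept, SD 25% and no gain from covariate adjustment.

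If the 80% rested on a smaller residual SD or another definition of the interaction, state that input and definition instead and show that it gives the figure.

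As a caution on interpretation, report the interaction as an estimate with its 97.5% confidence interval, and do not take a non-significant result as evidence of no interaction. The protocol already provides for confidence intervals at this level.

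The cost is wording only. The stated power becomes less favourable; the design, the sample size and the primary comparisons do not change, and no extra patients are needed.
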